### Laboratory procedures

Before a CVC, every included patient will be submitted to blood sampling for SCTs (PT, INR, aPTT and platelet count), ROTEM® analysis, serum fibrinogen, hemoglobin, hematocrit, ionized calcium and arterial pH. Blood samples of 5 mL will be obtained directly from a peripheral vein by applying a light tourniquet to avoid blood stasis, or from a central venous line after discarding the first 5 mL of blood (in the case of an indication for a second CVC, e.g., hemodialysis catheter), or from an arterial line. Blood samples for SCTs, ROTEM® and fibrinogen will be conditioned in citrate tubes (3.2%; Sarstedt Monovette®, Wedel, Germany) and processed immediately. Blood samples for hemoglobin level, hematocrit and platelet count will be conditioned in 2.6-mL tubes containing EDTA KE (Sarstedt Monovette®, Wedel, Germany).

Thromboelastometry analysis (ROTEM® delta, Pentapharm Co., Munich, Germany) will be performed by pipetting 300 μL citrated whole blood and 20 μL 0.2-M calcium chloride (CaCl_2_) with specific activators into a plastic cup [38]. Extrinsically activated (EXTEM), intrinsically activated (INTEM), and fibrinogen polymerization (FIBTEM) assays will be performed. ROTEM® analysis will run for up to 60 min. The parameters coagulation time (CT; s), clot formation time (CFT; s), maximum clot firmness (MCF; mm), alpha angle (α; degrees) and amplitude at 10 min (A10; mm) will be recorded [38].

The EXTEM assay contains a preparation of human recombinant tissue factor, which activates the coagulation cascade and can assess coagulation status via CT_EXTEM_, CFT_EXTEM_ and MCF_EXTEM_ [27]. The FIBTEM assay uses cytochalasin D which is a potent platelet inhibitor and serves to evaluate fibrinogen function and fibrin polymerization [27]. The A10 is a surrogate marker of MCF and can predict coagulopathy with high sensitivity and specificity (1.0 and 0.7, respectively) with the advantage of a faster evaluation of coagulation disorders [39].

Prothrombin time, INR and aPTT (ACL TOP 700 system, Instrumentation Laboratory, Bedford, MA, USA), serum fibrinogen (Clauss method) and platelet count (Sysmex® XN-Series, Sysmex Corporation, Lincolnshire, IL, USA) will be performed according to the hospital’s standard analytical methods.

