**Fig. 1 Fig1:**
[figure not shown]
Coagulogram-based blood transfusion protocol. *INR* international normalized ratio; *aPTT* activated thromboplastin time; *FFP* fresh frozen plasma

Accordingly, if INR ≤1.5, aPTT ≤50 s, platelet count ≥50,000/μL and serum fibrinogen ≥150 mg/dL, no transfusion is indicated. Otherwise, if INR >1.5 or aPTT >50 s, FFP is transfused at 10 mL per kg of body weight; and/or if platelet count <50,000/μL, 1 unit per 10 kg of body weight of random platelets (up to 10 units) or 1 unit of apheresis platelets is transfused; and/or if serum fibrinogen <150 mg/dL, 1 unit per 10 kg of body weight of cryoprecipitate is transfused (up to 10 units).

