### Thromboelastometry-based group

The thromboelastometry-based transfusion protocol uses EXTEM and FIBTEM assays from the ROTEM® and was adapted from Görlinger et al. [42] (Fig. 2). No transfusion is necessary when CT_EXTEM_ is ≤80 s and A10_EXTEM_ is ≥40 mm. The CT_EXTEM_ will be used to assess coagulation factor deficiency. For patients in whom CT_EXTEM_ is >80 s, transfusion of 10 mL per kg of body weight of FFP is performed. If the patient presents an A10_EXTEM_ <40 mm, we further evaluate the A10_FIBTEM_. If A10_FIBTEM_ is ≥10 mm (indicating adequate fibrinogen function), random platelet units (1 unit per 10 kg of body weight; maximum 10 units) or 1 unit of apheresis platelets is transfused. Otherwise, if A10_FIBTEM_ is <10 mm (indicating fibrinogen deficiency), cryoprecipitate (1 unit per 10 kg of body weight; maximum 10 units) is transfused.

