### Restrictive group

The restrictive transfusion protocol is also based on SCTs, but it uses wider transfusion triggers and it does not take into account serum fibrinogen and aPTT levels (Fig. 3). If INR is ≤5.0 and platelet count is ≥25,000/μL, no transfusion is required. If INR is >5.0, FFP is transfused at 10 mL per kg of body weight; and/or platelet count is <25,000/μL, random platelet units (1 unit per 10 kg of body weight; maximum 10 units) or 1 unit of apheresis platelets is transfused.

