### Study endpoints

The primary efficacy endpoint is the proportion of patients transfused with any blood product (i.e., FFP, platelets or cryoprecipitate) prior to CVC. The primary safety endpoint is the incidence of major bleeding within the first 24 h after catheter insertion. Major bleeding was defined according to the HEME tool [41]. According to the HEME tool, major bleeding is defined as overt bleeding with any of the following (in the absence of other causes): decrease in hemoglobin of 20 g/L or more, transfusion of 2 or more units of RBC with no increase in hemoglobin level, decrease in systolic BP by 10 mmHg or more while the patient is sitting up, spontaneous decrease in systolic BP of 20 mmHg or more or increase in heart rate by 20 bpm or more; bleeding at any one of the following sites: intracranial, intraspinal, intraocular, pericardial, retroperitoneal or intraarticular; or wound-related bleeding requiring an intervention.

The secondary efficacy endpoints will be: the proportion of patients transfused with each blood component and the infused volume of each blood component, hemoglobin and hematocrit levels before and up to 24 h after CVC, costs associated to blood product transfusion and laboratory tests, ICU and hospital length of stay, and ICU, 28-day and hospital mortality. Secondary safety endpoints will include: the incidence of minor bleeding complications (i.e., oozing or hematoma with no criteria for major bleeding) and the proportion of patients transfused due to bleeding within the first 24 h after CVC, and the incidence of acute transfusion-related adverse events (i.e., transfusion-associated cardiac overload, acute hemolytic transfusion reactions, anaphylactic reactions, febrile nonhemolytic reactions and urticarial reactions). The transfusion of bleeding patients after CVC will follow the Hospital Israelita Albert Einstein institutional transfusion protocol. Accordingly, if INR >1.5 or aPTT >32 s, FFP (10 mL per kg) is administered. If serum fibrinogen <150 mg/dL, cryoprecipitate (1 unit per 10 kg) or fibrinogen concentrate (2 to 4 g) is administered. If the platelet count <50 x 10^3^/mm^3^, random platelets (1 unit per 10 kg) or apheresis platelets (1 unit) are administered. Correction of hypothermia (axillary temperature ≥35 °C), hypocalcemia (ionized calcium ≥1.14 mmol/l) and acidosis (pH ≥7.31) is always recommended.

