### Randomization, allocation and blinding

Allocation sequence with random numbers will be computer-generated using random, varied size blocks and stratification by severe renal failure (i.e., hemodialysis program). The randomization sequence will be stored in individually separated and sequentially numbered opaque, sealed envelopes and kept secured in a locker with restricted access (centralized at ICU pharmacy). After the consent term is signed and coagulation tests collected, patients will be randomly assigned to study groups with an allocation ratio of 1:1:1.

Allocation concealment will be preserved by holding randomization sequence disclosure until the consent term is signed and coagulation tests collected. Patients will be enrolled by an on-call recruiter, and assignment to intervention will be provided by an independent researcher, who will be the only one to know which intervention the patient will be assigned to. The research subjects, central venous catheter inserter and outcome assessors will be blinded to the assigned intervention and bleeding will be assessed by the use of the HEME tool [41] immediately after CVC and 24 h after the procedure. The catheter inserter is not directly responsible for care of the patient included in the trial and will not have access to the patient’s chart. In case of major bleeding or serious transfusion-related adverse reaction, unblinding to the attending physician is anticipated.

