### Statistical analysis plan

All analyses will be performed as intention-to-treat. Categorical variables will be summarized as absolute and relative frequencies. Normality will be tested with the Kolmogorov-Smirnov test. Accordingly, continuous variables with normal distribution will be summarized as mean ± SD, or median and interquartile range (IQR) in case of non-normal distribution.

Comparisons between groups of continuous variables will be performed with one-way analysis of variance (one-way ANOVA) followed by Tukey’s test for multiple comparisons (for normally distributed variables), or the Kruskal-Wallis test followed by the Mann-Whitney *U* test (for non-normally distributed variables). Proportions between groups will be analyzed with the chi-square test or Fisher’s exact test, as appropriate.

All binary outcomes will be analyzed using a generalized linear model with binomial distribution and logit link function followed by pairwise comparisons adjusted by Bonferroni correction for multiple comparisons. Pairwise comparisons will be presented as odds ratio (OR) along with 95% confidence interval (95% CI), which will be calculated by logistic regression.

A survival curve will be performed with the Kaplan-Meier estimator and the log-rank test will be used to compare groups. To assess time-to-event (28-day mortality), an unadjusted Cox proportional hazards regression model will be performed. The hazard ratio (HR) with its respective 95% CI will be reported.

Prespecified subgroup analysis for the primary outcome will be presented as a Forest plot, and will include the presence of hypothermia (<35 °C), SAPS 3 score (≥50 points) and MELD score (≥25 points). Interaction between groups and each covariate will be assessed by multivariate logistic regression.

Two-tailed tests will be used and when *p* < 0.05, the test will be considered statistically significant. To account for multiple comparisons (Coagulogram-based versus Thromboelastometry-based, Coagulogram-based versus Restrictive and Thromboelastometry-based versus Restrictive), the α level will be adjusted to 0.0167.

We will make maximum effort to reduce missing data. We will use the multiple imputation method to handle missing data when necessary. The Statistical Package for the Social Sciences version 22.0 (IBM Inc., Chicago, IL, USA) will be used for statistical analyses. GraphPad Prism version 6.07 (GraphPad Software Inc., La Jolla, CA, USA) will be used for graph plotting.

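### The primary efficacy comparison names no baseline covariate, although the tests that determine each protocol's transfusion order are collected before randomization; the planned test is valid but gives up precision

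*Protocol article*

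**What the plan says.** Study endpoints defines the outcome: "The primary efficacy endpoint is the proportion of patients transfused with any blood product", counted before catheter insertion. Laboratory procedures has the tests done on everyone, whatever the arm: "Before a CVC, every included patient will be submitted to blood sampling for SCTs (PT, INR, aPTT and platelet count), ROTEM® analysis", with fibrinogen in the same draw. Randomization, allocation and blinding fixes the order of events: "After the consent term is signed and coagulation tests collected, patients will be randomly assigned to study groups".

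Each arm then applies a threshold rule to those values:
- Coagulogram-based: "if INR ≤1.5, aPTT ≤50 s, platelet count ≥50,000/μL and serum fibrinogen ≥150 mg/dL, no transfusion is indicated".
- Thromboelastometry-based: "No transfusion is necessary when CT_EXTEM_ is ≤80 s and A10_EXTEM_ is ≥40 mm".
- Restrictive: "If INR is ≤5.0 and platelet count is ≥25,000/μL, no transfusion is required".

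For the comparison, the Statistical analysis plan states: "All binary outcomes will be analyzed using a generalized linear model with binomial distribution and logit link function". Pairwise odds ratios follow, tested at 0.0167. Covariates appear only in the subgroup interactions (hypothermia, SAPS 3, MELD), and none of these is a trigger variable.

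**The concern.** Apart from departures from orders, whether a patient is transfused follows from the pre-randomization tests and the assigned rule. What all three rules would order is therefore known for every patient at baseline, including the two rules to which that patient was not assigned. A model without covariates treats the outcome as binomial noise within each arm. Much of its standard error then reflects which patients' INR, platelet count or clot firmness happened to fall in which arm, and not uncertainty about the strategies.

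At stake is power in a single-center trial of 165 patients. Its Discussion itself names incomplete recruitment and physicians' reluctance to follow a new protocol as risks. The information that would recover precision is already collected.

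**Working it through.** **Inputs from the article.** Sample size calculation: 90% v 65%, power 0.80, alpha 0.05, and 43 + 8 + 4 = 55 per group. Statistical analysis plan: two-sided tests, pairwise alpha 0.0167 (z = 2.393). I use n = 43 + 8 = 51 evaluable per arm, so N = 153 over three arms.

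**The plan's own figure.** With pooled variance, n = [1.960·√(2·0.775·0.225) + 0.842·√(0.90·0.10 + 0.65·0.35)]² / 0.25² = 42.6, so 43 per group. It reproduces.

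**Assumptions (not in the article).**
- d is the share of patients for whom thromboelastometry would order a product and the coagulogram would not. It is varied from 0 to 10%. Ten percent is the ceiling, because only 10% have no coagulogram order. For Coagulogram v Restrictive d is exactly 0: an INR above 5.0 is also above 1.5, and a platelet count below 25,000 is also below 50,000.
- e is the probability of departing from the rule, in either direction: 0, 5, 10 or 20%.
- The 90% and 65% are read as rates of orders. The rate given is then p(1 − e) + (1 − p)e.

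**Unadjusted standard error of the risk difference.** SE = √{[p₁(1 − p₁) + p₂(1 − p₂)]/51}, using the rates given. At e = 0: √(0.3175/51) = 0.079.

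**Standardized standard error.** Within each arm, take the proportion transfused by that arm's own order indicator and average over all 153 patients. Then SE² = 2e(1 − e)/51 + (1 − 2e)²·V/153, where V is the variance of the difference between the two order indicators: V = 0.25 + 2d − 0.25² = 0.1875 + 2d. At e = 0:
- d = 0: √(0.1875/153) = 0.035, ratio 2.25.
- d = 10%: √(0.3875/153) = 0.050, ratio 1.57.

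Power is Φ(difference/SE − 2.393). Ranges run over d.

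| Departures | Rates given | Difference | SE unadjusted | SE standardized | Width ratio | Power unadjusted | Power standardized |
|---|---|---|---|---|---|---|---|
| 0 | 90% v 65% | 0.250 | 0.079 | 0.035–0.050 | 1.57–2.25 | 0.78 | ≥0.99 |
| 5% | 86% v 63.5% | 0.225 | 0.083 | 0.053–0.063 | 1.33–1.55 | 0.62 | 0.89–0.96 |
| 10% | 82% v 62% | 0.200 | 0.087 | 0.066–0.072 | 1.21–1.32 | 0.47 | 0.65–0.74 |
| 20% | 74% v 59% | 0.150 | 0.092 | 0.082–0.085 | 1.09–1.13 | 0.22 | 0.27–0.29 |

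Simulation with 51 per arm agrees with these large-sample formulas. Standardized v unadjusted power was at least 0.99 v 0.77 at full adherence, 0.87–0.95 v 0.61 at 5%, 0.65–0.75 v 0.45 at 10%, and 0.29–0.32 v 0.22 at 20%.

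Reading down the table, part of the fall in both power columns comes from the smaller difference that departures produce. Only the gap between the two columns in a row is the cost of omitting the baseline tests.

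**Does adding the tests to the logistic model do the same?** No. In 400 simulated two-arm trials (55 per arm, one laboratory score driving both rules), the model separated or failed to converge in 99.5% at full adherence. With 10% departures the median log odds ratio moved from −1.06 to −1.50 and its standard error from 0.45 to 0.57. That is a conditional effect, not a sharper estimate of the marginal one.

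**The case against.** Several points against stand and limit the finding.

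- **The planned comparison is not wrong.** A randomized comparison without covariates keeps its type I error and its coverage. A reader might infer that chance imbalance in coagulopathy biases the result or produces excess false positives. The article does not support that: such imbalance is what alpha already covers. The interval is inefficient, not invalid.
- **The model does not cause a shortfall against the stated 0.80.** A reader might blame it for power of 0.77 to 0.78. That small gap comes from the sample size and the 0.0167 level.
- **Full adherence is the best case.** The article allows concomitant care and expects some resistance, and at 20% departures little gain is left.
- **The article is a condensed plan.** It uses the word unadjusted only for the Cox model, so for the logistic model this is the plain reading. A fuller plan could name covariates. The section does state its model for the endpoint, though, and that stated choice is what is assessed here.
- **The remedy changes the effect measure and needs care in small samples.** The standardized Wald test was mildly liberal in simulation (0.050–0.063 at nominal 0.05). A re-randomization p-value looks like a natural repair but is not one. It tests the hypothesis that no patient's outcome depends on the arm, whereas equal overall rates can arise from different patients being transfused. Its plain form was conservative (about 0.02–0.05 at nominal 0.05) and gave up much of the gain.

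What remains is that the strongest predictors of the primary outcome are measured before randomization in every patient and are not used.

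**Conclusion.** The point holds as a loss of precision, worth correcting but not a defect of validity. The gain is large if the protocols are followed closely, worthwhile up to about 10% departures, and small at 20%. It rests on the article's 90% v 65%, on departures being equally likely in both directions, and on inference to a wider patient population. For the enrolled patients alone, full adherence would make the difference between the rules known without error. The width ratio does not depend on whether 51 or 55 per arm is used. It does depend on the rates: for Coagulogram v Restrictive at full adherence, a Restrictive rate of 10% to 40% in place of 65% gives 1.84 to 1.99.

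**What to change.** In the Statistical analysis plan:

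1. Define for every patient, from the pre-randomization tests, three baseline indicators: whether the Coagulogram-based, Thromboelastometry-based and Restrictive protocols would each order any product.
2. Make the primary efficacy estimate a standardized marginal risk difference. Within each arm, take the proportion actually transfused by that arm's own indicator (cell means), and average over all randomized patients. The outcome stays the transfusion given, by intention to treat, so departures from orders do not bias it.
3. Use an influence-function (robust) standard error with a small-sample correction, and test at the same 0.0167. Add a marginal odds ratio if wanted.
4. State what is done if a cell is empty. Only about 0.10 × 51 = 5 Coagulogram patients are expected to have no order. State also which statistic the interim looks at 55 and 110 patients will use.
5. Keep the planned unadjusted odds ratio as a supporting analysis. Do not simply add the tests or the indicators to the logistic model, and do not take the p-value from re-randomization.

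The cost is plan wording and programming, with no new data. The downsides are a less familiar method, a mildly liberal test if the correction is left out, and imputed indicators where a baseline test is missing.

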## Background

Central venous catheterization (CVC) is a routine procedure in the intensive care unit (ICU) [1]. In the USA alone, more than 15 million catheter-days are reported annually [2]. Bleeding is the most common complication of CVC [3], with an incidence of between 12 per 1000 [4] and 94 per 1000 catheter insertions [5], and may be life-threatening in severe cases. More recently, the use of ultrasound guidance for CVC has significantly decreased overall mechanical complication rates [6–10] and is safe in patients with coagulopathy [11].

Patients with liver failure are classically believed to be prone to bleeding disorders [12]. Currently, approximately 9 out of 10 ICU physicians empirically transfuse liver failure patients before invasive procedures [13]. However, scientific evidence for this practice is lacking. Recent medical literature evidence now shows that patients with liver failure exhibit a rebalancing ability between anticoagulant and procoagulant factors [12] and have thrombin generation comparable to healthy individuals [14]. Thus, bleeding in those patients may be mainly related to circulatory and endothelial alterations instead of coagulation disorder per se. In spite of that, several physicians rely on standard coagulation tests (SCTs), i.e., prothrombin time (PT), international normalized ratio (INR), activated partial thromboplastin time (aPTT) and platelet count, to guide blood transfusion before CVC in patients with cirrhosis [15, 16].

It has been shown that SCTs reflect a limited view of coagulation status (isolated plasmatic component evaluation) [17, 18] and do not accurately predict bleeding risk in patients with suspected coagulopathy [18–21]. Specifically, patients with liver disease and prolonged PT/aPTT may have coagulation factor levels above the sufficient for adequate clot formation [22]. Moreover, attempts to correct (or normalize) standard coagulation tests by transfusion do not guarantee coagulopathy reversal [23, 24] and to insist on this practice may increase the risk of transfusion-related complications, including death [25].

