### Sample size calculation

We calculated the sample size based on the primary efficacy endpoint. We assumed a transfusion rate of 90% in the Coagulogram-based group (i.e., control group) [11] and an absolute risk reduction of 25% for the Thromboelastometry-based and Restrictive groups. Using a study power of 0.80 and alpha of 0.05, we need *n* = 43 patients per group. The sample size was adjusted for multiple comparisons (additional increase of 20%, *n* = 8 per group) (Coagulogram-based versus Thromboelastometry-based, Coagulogram-based versus Restrictive, and Thromboelastometry-based versus Restrictive) according to Witte et al. [43]. To account for loss to follow-up, we have added 10% (*n* = 4) more patients to the adjusted sample size. The final required sample will be 55 patients per group (total estimated sample size of 165 patients).

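### Binary outcomes have two prescribed methods with no rule between them, and the logistic odds ratio promised for major bleeding cannot be estimated if an arm has no event

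*Protocol article*

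**What the plan says.** Three statements in the article bear on this.

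- Under Study endpoints: "The primary safety endpoint is the incidence of major bleeding within the first 24 h after catheter insertion". This is a yes/no outcome per patient.
- Under Statistical analysis plan, on group comparisons: "Proportions between groups will be analyzed with the chi-square test or Fisher’s exact test, as appropriate".
- In the next paragraph of that section: "All binary outcomes will be analyzed using a generalized linear model with binomial distribution and logit link function", followed by Bonferroni-corrected pairwise comparisons. The effect measure is then fixed: "Pairwise comparisons will be presented as odds ratio (OR) along with 95% confidence interval (95% CI), which will be calculated by logistic regression".

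The section sets the level for the three pairwise comparisons at 0.0167. It does not rank the two methods for binary endpoints, does not say whether tests from the logistic model are Wald or likelihood-ratio, and names no method for an arm without events.

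On event rates, the Background cites catheter bleeding of any kind at 12 to 94 per 1000 insertions and says that ultrasound guidance has lowered mechanical complications. All insertions in this trial are ultrasound-guided (Central venous catheterization). No rate for major bleeding is given. The planned size is 55 per group, 165 in total (Sample size calculation).

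**The concern.** Major bleeding is only part of all bleeding, and the Discussion itself expects complications to become very rare under ultrasound guidance. An arm of 55 with no major bleed is therefore a realistic outcome. The logistic odds ratio between that arm and any other then has no finite maximum-likelihood value, and the usual interval around it carries no information. Yet this is the effect measure that the plan promises for every binary outcome, including a primary endpoint.

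At stake is the safety half of the trial's hypothesis, that the restrictive and thromboelastometry-guided strategies are safe. A reader needs an interpretable between-arm estimate of major bleeding. With two methods prescribed and no rule between them, the choice of what to report could also be made after the counts are known.

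**Working it through.** **1. The plan's own figure.** For 90% versus 65%, two-sided 0.05 and power 0.80, with pooled variance:

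n = [1.96 × √(2 × 0.775 × 0.225) + 0.8416 × √(0.90 × 0.10 + 0.65 × 0.35)]² / 0.25² = (1.157 + 0.474)² / 0.0625 = 42.6, so 43 per group.

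Adding the stated 8 and 4 gives 55 per group, and 3 × 55 = 165. The figure reproduces, and 55 per arm is used below.

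**2. How likely is an arm with no event?** For a common true rate p, the chance of no event in one arm is q = (1 − p)^55. The chance that at least one of three arms is empty is 1 − (1 − q)³, and that all three are empty is q³. The rates are assumptions; 1.2% and 9.4% are the ends of the Background range for bleeding of any kind.

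| Assumed rate per arm | q | At least one empty arm | All three empty |
|---|---|---|---|
| 0.5% | 0.759 | 99% | 44% |
| 1% | 0.575 | 92% | 19% |
| 1.2% | 0.515 | 89% | 14% |
| 2% | 0.329 | 70% | 4% |
| 5% | 0.060 | 17% | 0.02% |
| 9.4% | 0.004 | 1.3% | under 0.01% |

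At the interim looks after 55 and 110 participants (about 18 and 37 per arm), the chance of at least one empty arm is 97% and 85% at a 2% rate, and 78% and 39% at 5%.

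**3. What each method returns with an empty arm.** A binomial-logit model was fitted to two arms of 55, with these illustrative counts:

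| Events | Log odds ratio (SE) | Wald p | Likelihood-ratio p | Fisher p |
|---|---|---|---|---|
| 0 vs 2 | 21.3 (17,665) | 0.999 | 0.094 | 0.495 |
| 0 vs 5 | 22.3 (17,665) | 0.999 | 0.0074 | 0.057 |
| 0 vs 6 | 22.5 (17,665) | 0.999 | 0.0032 | 0.027 |
| 0 vs 7 | 22.6 (17,665) | 0.999 | 0.0014 | 0.0128 |
| 0 vs 8 | 22.8 (17,665) | 0.999 | 0.0006 | 0.0059 |

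The coefficient and standard error only show where the fitting algorithm stopped. The true maximum is at infinity, so the odds ratio and Wald interval carry no information in any row. Fisher's test falls below 0.0167 from 0 versus 7 upward. At 0 versus 5 and 0 versus 6 the likelihood-ratio test is below 0.0167 and Fisher's test above it, so the missing rule matters even between the two tests that work.

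**4. Does an alternative give a usable interval?** The Newcombe 95% interval for a risk difference combines two Wilson intervals. For 0/55 the Wilson limits are 0 and 1.96² / (55 + 1.96²) = 0.065. For 7/55 = 0.127 they are 0.063 and 0.240.

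- 7 vs 0: difference 12.7 points. Lower limit 0.127 − √[(0.127 − 0.063)² + 0.065²] = 0.036; upper limit 0.127 + (0.240 − 0.127) = 0.240. The interval is 3.6 to 24.0 points.
- 0 vs 0: difference 0, interval −6.5 to 6.5 points.

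Both can be interpreted, including the case where no arm has an event and no pairwise odds ratio exists.

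**The case against.** The strongest reply is that the plan already contains a test that works. The sentence on proportions allows Fisher's exact test where suitable, which is the customary provision for sparse cells, and it gives p = 0.0128 for 0 versus 7. That stands. A reader might infer from the logistic wording that the planned analysis would return a p-value near 1 in the face of a real excess and so conceal harm. The article does not support this: a p-value near 1 is a property of Wald tests, which the plan does not specify, and the likelihood-ratio test of the same model gives 0.0014. Event frequencies will be reported in any case, and serious adverse events go to the monitoring board at once.

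The illustration also needs care. Empty arms are likely when the rate is low in every arm, whereas 7 of 55 is 12.7%. At a true rate of 2%, 7 or more events in an arm has probability of about 0.0001. With the counts to be expected at low rates, such as 0 versus 2, Fisher's test gives p = 0.50 and detects nothing either. The gain from changing method at low rates is thus an interpretable estimate, not more power.

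The event rate is assumed, and the endpoint definition is broad. If major bleeding approached 5% to 9.4%, the difficulty would largely disappear.

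Finally, sparse-data handling can be left to a separate analysis plan. But the article does not leave the effect measure open: it fixes a logistic odds ratio for every binary outcome, and Fisher's test as worded supplies no replacement interval.

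**Conclusion.** The point holds at moderate severity. Two methods are prescribed for binary outcomes without a governing rule. For the primary safety endpoint, the specified odds ratio and interval would be unusable for at least one arm's comparisons with probability 70% to 99%, if the true major-bleeding rate is 0.5% to 2% per arm. This rests on that assumed range, a common rate across arms and 55 analysed per arm; at 5% the probability is 17%, and at 9.4% it is 1.3%. What is lost is the estimate, its interval and any Wald test. Valid hypothesis tests remain available within the plan.

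A reader might extend the point to the primary efficacy endpoint, where an arm at 0% or 100% transfused would cause the same failure. On the plan's own figures this is negligible: at 90% transfused, the chance that all 55 are transfused is 0.9^55 = 0.3%, and at 65% it is effectively nil.

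**What to change.** In the Statistical analysis plan section, or in the full analysis plan with a matching clarification, state the following.

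- **Major bleeding and other sparse safety outcomes** (minor bleeding and acute transfusion reactions where counts are zero or close to it): the decisive pairwise test is Fisher's exact test, or a named exact unconditional test, with the unadjusted p-value compared once against 0.0167.
- **Effect measure for these outcomes:** the pairwise risk difference with a Newcombe or Miettinen-Nurminen interval. If an odds ratio is wanted as well, take it from Firth's penalised logistic regression.
- **Primary efficacy endpoint:** keep the logistic model as the governing analysis and say so, with chi-square or Fisher as supportive only.

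The decision should be recorded before anyone who writes the analysis sees outcome data by arm. The change needs no extra patients or data. It costs slightly more analysis work, some of it possibly outside SPSS 22. Exact tests are also conservative, as the 0 versus 5 and 0 versus 6 rows show; that should be accepted knowingly, or an exact unconditional test chosen in advance.
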